### Study design

2.2.

This is an international, pan-specialty, collaborative cross-sectional survey. A global panel of experts will form the study steering committee (SSC), providing a consensus-based approach to survey development, validation, and distribution. This study will be reported in line with the checklist for reporting of survey studies (CROSS) and the checklist for reporting results of internet E-surveys (CHERRIES) (16, 17). Ethical approval is provided by the Hull York Medical School Ethics Committee (REF22-23 10).

To collect data, the survey will be delivered electronically online using the Qualtrics^XM^ Platform™, Utah, USA. The format will be designed to include a combination of binary, Likert or multi-select. Free text comments will be used to collect further detail but will be kept to a minimum to help ensure good completion rates.

### Questionnaire development

2.3.

A pilot questionnaire will be developed based on SSI prevention measures outlined in the CDC (2017), WHO (2018), NICE (2019), Wounds UK (2020) and the International Surgical Wound Complications Advisory Panel (ISWCAP) guidelines. Additionally, feedback from the survey of surgical site infection prevention practice in UK vascular surgery will be used to inform survey questions/design (12–14, 18, 19). Since the survey will be targeting participants across multiple specialties, it will only contain general prevention measures widely applicable. A draft survey will be provided in Supplementary Material 1.

The questionnaire will be structured into five sections; demographics, SSI surveillance, preoperative, peri-operative and postoperative SSI prevention domains. Data will be collected on participant surgical specialty, operative grade, country of practice and financial healthcare system of practice. SSI data will include criteria used for diagnosis. There were 15 perioperative domains formulated the UK questionnaire, which will be scrutinized against the CDC, WHO, NICE and ISWCAP guidelines outlined above by the SSC, to form a pilot questionnaire. The process of questionnaire development will be carried out through discussion by members of the SSC and a record of any question refinement will be documented. The number of questions will not be rigidly defined but the SSC will consider the impact on survey duration which can influence completion rates.

The pilot questionnaire will be distributed to at least two consultants of each surgical specialty; vascular, general, orthopedic and trauma, urology, plastic and reconstructive, cardiothoracic, neurosurgery and otolaryngology for multiple rounds of validation. After each round feedback will be analyzed by the SSC and consensus-based changes will be adopted. Any alterations will be done so on unanimous decision and documented as major (questions removed or added), and minor (wording alterations). The survey will be validated further in subsequent rounds until the SSC agrees no further alterations are required.

### Sample characteristics

2.4.

The survey will be sent out electronically to surgeons of any specialty and at all levels of training worldwide. This includes consultants, and surgical trainees (specialties registrars/residents). To be included in the study, surgeons must be currently practicing and be registered with the national surgical body/college/society. The validated online survey will be distributed through Qualtrics^XM^ for single-stage cluster sampling in addition to dissemination through social media, where snowballing may occur. Each network of distribution will provide a cluster, i.e., VERN for the vascular surgeons and PIACO group for general surgery. The study population will provide a representation of existing SSI preventative measures used worldwide.

Given the global nature of the survey, no sample size will be calculated. Raking will be used to assign weight values to each survey respondent in such a manner, that the weighted distribution of the sample is in very close agreement with two or more marginal control variables. Socio-economic (developing vs. developed countries) variables and surgical specialties will be used to weigh the sample of responses. As such, results will be able to be extrapolated into wider populations, irrespective of the distribution of responses received.

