**Methods:**

This collaborative cross-sectional survey will be aimed at pan-surgical specialties internationally. The study has been designed and will be reported in line with the CROSS and CHERRIES standards. An international study steering committee will design and internally validate the survey in multiple consensus-based rounds. This will be based on SSI prevention measures outlined in the CDC (2017), WHO (2018), NICE (2019), Wounds UK (2020) and the International Surgical Wound Complications Advisory Panel (ISWCAP) guidelines. The questionnaire will include demographics, SSI surveillance, preoperative, peri-operative and postoperative SSI prevention. Data will be collected on participants' surgical specialty, operative grade, of practice and financial healthcare system of practice. The online survey will be designed and disseminated using Qualtrics^XM^ Platform™ through national and international surgical colleges and societies, in addition to social media and snowballing. Data collection will be open for 3 months with reminders, and raking will be used to ascertain the sample. Responses will be analyzed, and the chi-square test used to evaluate the impact of SSI prevention variables on responses.

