### Survey administration

2.5.

The survey will be advertised in weekly rounds, 1 month prior to dissemination using affiliated society social media accounts and the Surgical Infection Research Network Twitter account (@SIRNglobal).

The survey will be disseminated worldwide, with an international SSC to establish a network of distribution. The committee has been involved in previous successful surveys and collaborative projects through the PIACO group, the Vascular Endovascular Research Network (VERN), James Lind Alliance (JLA) and ISWCAP surveys (20–23). The committee will also identify new routes of distribution within this project. The validated online survey will be distributed using an electronic link. Participants will receive an email via their affiliated membership organization, inviting them to take part and will include a direct link to the online survey. Following the invitation, surgeons will have 3 months to complete the survey, with reminders sent every 2 weeks. The survey will also be promoted via social media platforms, using the SIRN Twitter account in addition to affiliated organization accounts. The “prevent multiple submissions” option in Qualtrics will be enabled to prevent multiple participation of participants. A secondary IP address check will follow to ensure there are no remaining duplicate entries. No two entries from the same IP address will be allowed within 24 h. After the data collection window, the survey will lock out, preventing further responses. Participants will be offered an opportunity to win a £20 Amazon voucher as an incentive to participate in the survey. Survey items will not be randomized to improve participation, as the logical order of each survey section was unanimously agreed by the SSC to improve the response flow. Adaptive questioning will be used depending on the following questions from a response. The number of items and screens or pages on mobile and personal computers will be reported in the manuscript write-up.

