### Limitations

3.1.

Reminders will be sent on a 2-weekly basis to increase the response rate and to prevent sampling bias. Additionally, the study will be advertised on its own Twitter account to gain attention. Response fatigue is a common issue, leaving some questions unanswered. To keep this to a minimum, the survey has been designed to only ask relevant questions and to be succinct, clear, and unambiguous.

Due to the nature of the study, there is room for responder and recall bias. To minimize this, questions wording and survey length have been considered carefully during all steps of the development of the survey. Questions will be categorized into SSI-related preoperative, perioperative, and postoperative themes to preserve the structure and enable ease of organization for respondents to follow.

Additionally, there may be discrepancies in the response rates between different countries, not providing an accurate representation of certain regions. There may also be different local/national guidelines and unequal access to certain resources depending on the geographical regions. As this survey will be delivered worldwide, questions are based on guidelines from the National Institute for Health and Care Excellence (NICE), Centers for Disease Control and Prevention (CDC) and World Health Organization (WHO). These guidelines are internationally recognized and available, therefore discrepancies between geographical regions and differences in local guidelines should be kept to a minimum.

There is no standardized consensus recommendation on SSI prevention regarding perioperative practice. Unsurprisingly this can lead to a discrepancy in clinical practice, as shown by a questionnaire study within the UK (15). If international and pan-surgical SSI prevention practices also vary, guidance recommended by international bodies is not being followed. This may be due to the lack of underlying evidence for SSI prevention practice, and thereby the necessity for high-quality RCTs to establish the best practice for patients and surgeons worldwide.

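### The survey is labelled single-stage cluster sampling but is a non-probability sample, and recruitment route, which may be partly confounded with specialty, is not among the data listed for collection

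*Protocol article*

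**What the plan says.** - **Design label.** Protocol article, section 2.4 (Sample characteristics), describes distribution for "single-stage cluster sampling in addition to dissemination through social media, where snowballing may occur".
- **What a cluster is.** The same section: "Each network of distribution will provide a cluster, i.e., VERN for the vascular surgeons and PIACO group for general surgery".
- **How networks enter.** Section 2.5 (Survey administration): "The survey will be disseminated worldwide, with an international SSC to establish a network of distribution", followed later by "The committee will also identify new routes of distribution within this project". No list of eligible networks and no random selection from one is described.
- **Other channels.** The abstract sends the survey "through national and international surgical colleges and societies, in addition to social media and snowballing". Section 2.5 adds email invitations through membership organisations.
- **The link.** Section 2.5: "The validated online survey will be distributed using an electronic link".
- **Data and weighting.** The respondent characteristics listed in section 2.3 are specialty, grade, country and funding system. Section 2.4 rakes on development status of the country and on specialty. Recruitment route appears in neither list.
- **Reminders.** Section 3.1 (Limitations): "Reminders will be sent on a 2-weekly basis to increase the response rate and to prevent sampling bias".
- **Objective affected.** Section 2.1 makes variation within and between specialties a secondary objective. The primary objective concerns barriers to standardised practice.

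**The concern.** Single-stage cluster sampling is a probability design: clusters are drawn by a known random mechanism from a list of clusters, and everyone in the selected clusters is approached. A reader who sees that label will assume known inclusion probabilities and a defined population. Neither exists if a committee picks the networks, the list stays open and part of the sample arrives through social media.

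The reminder statement has a similar fault. Sampling or coverage bias depends on who receives the invitation. A reminder cannot reach a surgeon outside every network and outside the accounts that advertise the survey.

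The practical stake is the inter-specialty comparison. If vascular surgeons come mainly through a vascular research network and another specialty comes mainly through open advertising, a difference in reported practice may reflect who joins a research network as well as specialty. Unless route is recorded, nobody can tell how much.

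**Working it through.** The article gives no sample size, number of networks, response rate or error level, so there is no figure of its own to reproduce. The check is mostly a comparison of statements. The two numerical illustrations rest on assumed values.

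**1. Label against procedure**

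| Feature of single-stage cluster sampling | What the article describes |
|---|---|
| A frame of clusters | None; the committee establishes the networks (2.5) |
| Random selection of clusters | None described; new routes may be added (2.5) |
| Every respondent belongs to a sampled cluster | Not so for social-media and snowball recruits (2.4) |

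None of the three features is present, so inclusion probabilities are unknown.

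**2. Reminders.** They can change the proportion responding among those already reached. They leave the set of people reached unchanged, so they cannot prevent bias from coverage.

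**3. Whether raking removes a route effect.** Raking on two margins gives each respondent a weight equal to a specialty factor times a development-status factor. Within a cell defined by specialty and development status, all weights are equal. The weighted proportion in that cell therefore equals the unweighted one, and its mix of routes is unchanged. A route imbalance between specialties survives the weighting.

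**4. Possible size of a route effect (assumed values).** Let d be the difference in use of a measure between network and open recruits, the same in both specialties. Let s1 and s2 be the network-recruited shares of the two specialties. With no true specialty difference, the apparent difference is (s1 − s2) × d.

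| s1 − s2 | d = 5 points | d = 10 points | d = 15 points |
|---|---|---|---|
| 0.10 | 0.5 | 1.0 | 1.5 |
| 0.30 | 1.5 | 3.0 | 4.5 |
| 0.50 (0.80 − 0.30) | 2.5 | 5.0 | 7.5 |

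The range runs from negligible to material, and nothing in the article says where the survey will fall.

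**5. Response rate (assumed values).** Suppose 5000 surgeons are emailed and 500 reply, a true email-route rate of 500/5000 = 10%. If open recruits make up a share s of all replies and are pooled over the email denominator, the apparent rate is [500/(1 − s)]/5000:

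- s = 0.20: 625/5000 = 12.5%
- s = 0.40: 833.3/5000 = 16.7%
- s = 0.60: 1250/5000 = 25.0%

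The open part has no denominator, so a pooled rate has no meaning. The email-route rate can be recovered only if list sizes and route are both known.

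**The case against.** The best defence is that these are two loose phrases in a condensed article. No variance formula or weight is derived from the cluster label. The article's claim that results can be extrapolated follows from raking. Section 3.1 already admits responder bias and uneven national response. Link set-up and route tracking are operational details that the full protocol may contain, and sensitivity analyses usually sit in an analysis plan. Much of this stands. The silence on route tracking is not in itself a fault, and the label should not be blamed for the extrapolation claim.

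Four stronger readings are tempting, and the article does not support them:

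- **Specialty and network are completely aliased.** Only two networks are named, as examples. Colleges, societies, social media and later routes are not said to serve a single specialty, and specialty is asked of each respondent. One vascular surgeon recruited through a general college breaks complete collinearity. Confounding may be partial and its degree is unknown.
- **One common link serves all routes, so route is lost.** The text mentions an electronic link but does not say that it is the same for every route.
- **No response rate can be computed.** Emailed invitations go through membership organisations, so a denominator can exist for that part.
- **Specialty is the main contrast.** It belongs to a secondary objective.

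What the defence does not remove is that the label and the reminder claim are wrong as written. Neither is an omission that a fuller document could supply.

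**Conclusion.** The point holds in a limited form. Two statements are incorrect: the sample is not a single-stage cluster sample, and reminders do not prevent sampling bias. These conclusions need no assumptions beyond the text.

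It also follows that inter-specialty differences may be partly confounded with recruitment route, that the planned raking would not correct this, and that no overall response rate can be given. The size of the confounding cannot be derived from the article. The 7.5-point figure is the top of an assumed range that starts at 0.5 points, and it should not be read as an estimate. The primary objective is not a contrast between specialties, so the confounding point does not bear on it in the same way. The correction is worth making because it is cheap and because route is hard to recover reliably once responses are in.

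**What to change.** 1. In section 2.4, describe the sample as non-probability (networks chosen by the committee, plus open recruitment) and remove the term single-stage cluster sampling.
2. In section 3.1, limit the reminder claim to reducing non-response among those already invited.
3. Before launch, issue a separate link for each network and one for social media. Add a single item asking how the respondent received the survey, to catch forwarded links.
4. Obtain list sizes from the emailing organisations and report response rates for emailed routes only. Report open-route replies as counts.
5. For the inter-specialty comparisons, add a sensitivity analysis restricted to emailed respondents or presented by route.

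The cost is a little more set-up work with each society, one extra question and some rewording. If the full protocol already provides for route-specific links, only the wording, the reporting rule and the sensitivity analysis remain.

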## Discussion

3.

Current SSI prevention practice in UK Vascular surgery varies considerably, with little consensus on many measures (15). SSI prevention guidelines recommended by international bodies (12–14), include over 15 generic methods of preventing SSIs. Some of them are supported by evidence from randomized control trials (RCTs), such as avoiding razors for preoperative hair removal and the decolonization with intranasal antistaphylococcal agents for high-risk procedures. Both methods have been shown to reduce the SSI rate. The use of the WHO surgical checklist leads to a lower SSI rate after its implementation. The exact mechanism of this is suspected to be multifactorial (6). Multiple guidelines (12–14) recommend using antiseptic skin agents, though specific recommendations vary. Using alcohol-based chlorhexidine reduces the risk of SSI compared with aqueous iodine (24). Body surface warming systems to maintain normothermia perioperatively have strong evidence in preventing complications of hypothermia and lowering SSI rates (25). Postoperative negative pressure wound therapy decreases SSI rates in vascular surgeries but was not associated with a statistically significant decrease in SSI rates in other surgical disciplines (6). Antibiotic prophylaxis is recommended by all guidelines (12–14), RCTs focusing on vascular surgery demonstrated a significant reduction in SSI rate (26, 27). Although there are no RCTs on the effect of perioperative glycemic control and its impact on SSI rates, this is recommended in all major guidelines (6, 12–14). Retrospective studies do however confirm a higher risk of SSI rates in patients with postoperative hyperglycemia (6).

The incidence of SSI varies across surgical procedures, specialties, and conditions. Diagnostic and reporting challenges make true SSI rates difficult to capture. SSI rates are reported to vary from 0.1% to 40%. There are several patient- and procedure-related factors that influence the incidence of SSI. Patient comorbidities, advanced age, frailty and surgical complexity can increase the risk of developing an SSI. Additionally, prolonged duration and classification of the surgery are important procedure-related factors (28).

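### The survey collects only surgeons' and trainees' own reports, but the protocol states the result as measures in use worldwide and reads variation as non-adherence to guidance

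*Protocol article*

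**What the plan says.** Section 2.4 (Sample characteristics) defines the respondents: "The survey will be sent out electronically to surgeons of any specialty and at all levels of training worldwide". Consultants and trainees are both included, and no other staff group is named. Section 2.2 (Study design) gives the only data source: "To collect data, the survey will be delivered electronically online using the Qualtrics^XM^ Platform™, Utah, USA". On item format it says: "The format will be designed to include a combination of binary, Likert or multi-select", with sparing use of free text. Section 2.3 describes the content: "The questionnaire will be structured into five sections; demographics, SSI surveillance, preoperative, peri-operative and postoperative SSI prevention domains". Items are drawn from published guidelines, and operative grade is collected.

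Two statements then go from answers to practice. Section 2.4 says: "The study population will provide a representation of existing SSI preventative measures used worldwide", and adds that raked results can be extrapolated to wider populations. The Background of the Abstract has a similar aim. The last paragraph of section 3.1 (Limitations) reasons that, if practice varies across countries and specialties, the international bodies' guidance is not being observed.

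Section 3.1 does acknowledge possible bias from responders and from recall. Its answer is: "To minimize this, questions wording and survey length have been considered carefully during all steps of the development of the survey".

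**The concern.** The quantity of interest is what is done to prevent infection. The quantity measured is what surgeons say is done. The protocol treats the two as the same in its claim about measures in use and in its inference about adherence.

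Two mechanisms can separate them. Respondents may report a recommended measure that is not reliably carried out. They may also not know whether a measure is carried out, and guess. The second is plausible for measures such as the one in the Discussion: "Body surface warming systems to maintain normothermia perioperatively have strong evidence in preventing complications of hypothermia and lowering SSI rates". Other staff may deliver warming, although the document does not say who does.

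Both secondary objectives concern variation: within and between specialties, and across financial systems and economic classes. Errors in reporting act directly on those contrasts. A reader who takes the stated conclusion at face value could believe that practice is more uniform, or more varied, than it is.

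**Working it through.** The document gives no rate of use, misreporting rate, sample size or significance level, so there is no figure of its own to reproduce. All rates below are assumptions, chosen to show how the error behaves.

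**1. Equal over-reporting in both groups.** Let p be true use and q the share of non-users who report use, with all users reporting correctly. Reported use = p + (1 − p)q, so the reported difference is (1 − q) times the true one.
- True use 70% v 50%, q = 0.3: 0.70 + 0.30 × 0.3 = 0.79 and 0.50 + 0.50 × 0.3 = 0.65. The 20-point difference is reported as 14.
- q = 0.1, 0.2 and 0.4 give 18, 16 and 12 points.

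Now let only 95% of users report use: reported use = 0.95p + (1 − p)f, where f is the share of non-users who report use. The difference is multiplied by (0.95 − f).
- True use 80% v 60%, f = 0, 0.1, 0.2, 0.3, 0.4: 19, 17, 15, 13 and 11 points against a true 20.

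**2. Unequal over-reporting, equal practice.** True use is 60% in both groups, so reported use = 0.57 + 0.4f. The first group has f = 0.1, giving 0.61.
- Second group f = 0.2, 0.3, 0.4: 0.65, 0.69, 0.73. The false gaps are 4, 8 and 12 points.
- Chance that a two-sided 5% comparison of two proportions declares the gap significant: about 0.13, 0.39 and 0.73 with 200 per group, and about 0.26, 0.76 and 0.98 with 500 per group. A larger sample makes the false finding more likely.

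**3. Lack of knowledge that differs by grade.** Let k be the share who do not know and g the share of those who answer yes. Reported use = (1 − k)p + kg.
- p = 0.6, g = 0.8, k = 0.4 in trainees and 0.1 in consultants: 0.6 × 0.6 + 0.4 × 0.8 = 0.68 and 0.9 × 0.6 + 0.1 × 0.8 = 0.62, a false gap of 6 points.
- k = 0.3 v 0.1 with g = 0.8 gives 4 points; k = 0.5 v 0.1 with g = 0.9 gives 12.
- Grade is not a planned contrast, so this reaches the specialty comparison only through grade mix. If two specialties have 40% and 20% trainees (assumed), the false difference is 0.2 × 6 = 1.2 points, or 0.2 × 12 = 2.4 at the extreme.

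**4. What raking does.** The weights use specialty and development status. They change how much each respondent counts and leave each answer as given. Within a given specialty and development class, reported use still carries the errors above. Grade is not a named raking variable, so differences in grade mix are not removed either.

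**5. What validation does.** Section 2.3 sends the pilot to two or more consultants in each of eight specialties, over several rounds. This may reveal items that are hard to answer. It does not compare answers with practice, and trainees are not named among those consulted.

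**The case against.** Self-report is inherent in a design openly labelled a survey, and the protocol concedes bias from responders and recall. The primary objective is barriers to standardization; variation in practice is secondary. The guidelines disagree on several measures, so there is often no single recommended answer to over-report. The group's earlier UK vascular survey, also a questionnaire, found considerable variation, so self-report did not hide it there. All of this is fair, and it limits the weight of the point. It does not rescue the two statements: a general admission of bias does not limit a claim about measures in use or an inference about adherence.

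A reader might go further and infer that the questionnaire forces respondents to guess. The document does not support this. The draft is in Supplementary Material 1, which is not shown, and a do-not-know option may be there. Free text and adaptive questioning are also planned. Nor does the document establish that other staff deliver warming or glycemic control; that is an inference from the measures discussed.

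**Conclusion.** The point holds as one about what the survey may conclude. Answers from surgeons and trainees, unchecked against practice, support statements about reported practice. They do not support the section 2.4 claim about measures in use or the section 3.1 inference about adherence, and neither raking nor the pilot rounds closes that gap.

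The size is unknown. Under the assumed rates, a true 20-point difference is reported as 11 to 19 points, and false gaps of 4 to 12 points can arise between groups that misreport differently. Through grade mix alone, the false gap between specialties is only about 1 to 2 points. It would be tempting to conclude that the reported variation will be wrong, or wrong in a known direction. That does not follow: equal misreporting shrinks differences, unequal misreporting can act either way, and the document gives no rates.

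**What to change.** 1. In section 2.4, and in the matching aim in the Abstract, describe the result as a representation of *surgeon-reported* preventive measures.
2. In section 3.1, limit the inference about guidance to reported practice, and name over-reporting of recommended measures and lack of knowledge as limitations.
3. Repeat the specialty and economy comparisons in consultants only as a sensitivity analysis, using the grade already collected. This addresses grade mix; it does not correct over-reporting, for which the narrower wording is the remedy.
4. Before launch, confirm that items on measures the respondent may not control offer a do-not-know answer, and add one if it is absent. After data collection, guesses can no longer be separated from knowledge.

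The cost is a few sentences of wording, one check of the questionnaire and one extra table. The downside is a narrower claim, and fewer respondents in the consultant-only comparison.

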### Objectives

2.1.

Primary objective:
-To identify the barriers to establishing standardized SSI prevention practice.Secondary objectives:
-To identify intra- and inter-specialty variations in surgical site infection prevention practice.-To identify variations in practice amongst financial systems such as state and privately funded healthcare systems and economical classifications.

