Given the inconsistency in guidelines on how to prevent SSIs, there is a need for standardization. This survey will investigate the disparity in SSI preventative measures between different surgical fields and countries. It will ascertain whether surgeons could feasibly participate in recruiting to platform randomized controlled trials assessing multiple interventions, including antibiotic prophylaxis.

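### The survey's worldwide scope is not a valid reason to omit any size or precision statement, and with chi-square as the only named test a finding of variation will depend on group size as much as on practice

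*Protocol article*

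**What the plan says.** On size, section 2.4 (Sample characteristics) has one sentence: "Given the global nature of the survey, no sample size will be calculated". It then turns to raking on economic development and specialty, so that "the weighted distribution of the sample is in very close agreement with two or more marginal control variables". From this it concludes that findings will carry over to wider populations whatever mix of replies comes in.

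Recruitment is limited by time: "Data collection will be open for 3 months with reminders" (abstract, Methods). The article gives no expected number of replies, overall or by group.

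The secondary objectives in section 2.1 are comparative: "To identify intra- and inter-specialty variations in surgical site infection prevention practice" and "To identify variations in practice amongst financial systems such as state and privately funded healthcare systems and economical classifications". The Discussion adds countries: "This survey will investigate the disparity in SSI preventative measures between different surgical fields and countries". The abstract names one test, with "the chi-square test used to evaluate the impact of SSI prevention variables on responses". Section 2.3 lists eight specialties for piloting: "vascular, general, orthopedic and trauma, urology, plastic and reconstructive, cardiothoracic, neurosurgery and otolaryngology".

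Limitations (3.1) accepts that response rates may differ between countries. It also says that if practice varies internationally and across specialties, international guidance is not being followed.

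**The concern.** This is a stated decision with a stated reason, not a detail left to a fuller document, and the reason is wrong. A worldwide target population does not prevent a precision calculation, because population size barely enters it.

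The consequence lies in the secondary objectives. They compare groups whose sizes nobody controls, the only named tool is a significance test, and no difference worth calling variation is fixed. In very large groups a small difference will be significant and can be read as guidance not being followed. In small groups a large difference will often be missed and can be read as uniform practice. Raking, which the article brings in directly after declining a sample size, cannot repair this because it adds no respondents.

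**Working it through.** The plan states no sample size, so there is no figure to reproduce. It also gives no significance level, power, expected proportions, reply numbers or population margins. The following are therefore **assumptions**: two-sided 0.05, 50% in the reference group and, unless weighting is mentioned, unweighted independent replies.

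**1. Does a global population matter?** For a half-width of 5 points, n0 = 1.96² × 0.25 / 0.05² = 384.2. With the finite population correction, n = n0 / (1 + (n0 − 1)/N):
- N = 20,000: 384.2 / 1.0192 = 377
- N = 2,000,000: 384.2 / 1.0002 = 384

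A hundredfold larger population adds 7 respondents.

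**2. Precision within one group.** Half-width = 1.96 × √(0.25/n):
- n = 20: 21.9 points
- n = 100: 9.8 points
- n = 400: 4.9 points
- n = 1,000: 3.1 points

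**3. Chance that chi-square is significant.** For equal groups of n and difference d, power = Φ[(d√n − 1.96√(2p̄(1−p̄))) / √(p1(1−p1) + p2(1−p2))].

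For 50% vs 60%, p̄ = 0.55:
- n = 100: (1.000 − 1.379)/0.700 = −0.54, so 29%
- n = 1,000: (3.162 − 1.379)/0.700 = 2.55, so 99.5%

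| True difference | Group sizes | Significant |
|---|---|---|
| 10 points | 50 vs 50 | 17% |
| 10 points | 100 vs 100 | 29% |
| 10 points | 400 vs 400 | 81% |
| 10 points | 1,000 vs 1,000 | 99.5% |
| 20 points | 20 vs 20 | 25% |
| 20 points | 400 vs 20 | 41% |
| 20 points | 100 vs 100 | 83% |
| 5 points | 2,000 vs 2,000 | 89% |

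The same 10-point difference runs from usually missed to almost always declared. At a fixed 100 per group the result also depends on the difference itself (29% for 10 points, 83% for 20).

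**4. Precision of a contrast.** For 50% vs 60%, half-width = 1.96 × √((0.25 + 0.24)/n): 13.7 points at 100 per group and 4.3 points at 1,000 per group. An interval shows the reader this; a p-value does not.

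**5. What raking does to a pooled figure.** Take one margin, with developing countries supplying a share r of replies against a target share t. The Kish design effect is t²/r + (1−t)²/(1−r). With t = 0.50 (assumed):
- r = 0.10: 2.500 + 0.278 = 2.78, so 1,000 replies are worth 1,000/2.78 = 360
- r = 0.05: 5.000 + 0.263 = 5.26, so 1,000 replies are worth 190

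The pooled half-width widens from 3.1 points to 1.96 × √(0.25/360) = 5.2, or 1.96 × √(0.25/190) = 7.1. In this example weights are constant within each economic group, so the contrast between the two groups loses nothing. The loss falls on the pooled estimate.

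**The case against.** The strongest defence is that an open survey with a fixed window takes what it gets and can reasonably report the precision achieved. That would be acceptable, but the article does not argue it; it gives worldwide scope as the reason. The proposed change adopts this defence.

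Second, the abstract's sentence on chi-square does not say that every specialty or economic group will be tested, and the list of contrasts may sit in a document not shown. This stands as a limit: the article states no decision rule. It does set comparative objectives, names only this test, and attaches a strong inference to variation.

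Third, the primary objective, identifying barriers, is descriptive. This stands: it needs only a precision statement.

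Fourth, one might want a fixed minimum group size or a cap on weights. Neither follows from the documents, and round figures do not do the job. With a 100-reply minimum, a 10-point contrast still has 29% power and an interval of about ±14 points. With weights capped at 5 times the mean, the 10% example is unchanged, since its weight is 0.50/0.10 = 5. In the 5% example the needed weight is 10, and the cap leaves developing countries at about 25–33% of the weighted sample against the assumed 50%. These are trade-offs for the investigators.

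Fifth, simple-random-sample figures ignore the network clusters and snowballing in section 2.4. That is correct. The working is illustrative, and the reported intervals should allow for clustering where possible.

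**Conclusion.** The point holds. The reason for omitting a size or precision statement is invalid, and group size will influence the comparative findings as much as practice does: under the stated assumptions, a 10-point difference is significant 29% of the time at 100 per group and 99.5% at 1,000. Raking does not help small groups and could reduce 1,000 replies to an effective 360 for pooled estimates. That figure rests on an assumed 50% target and 10% reply share, since the article gives no margins.

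The documents do not support four stronger readings that a reader might infer:
- **That results follow group size instead of practice.** The test responds to both, as the 29% and 83% at 100 per group show.
- **That raking inflates small specialties as such.** A weight reflects sample share against target share, so a specialty with few replies may be weighted down.
- **That the effective 360 applies to comparisons between groups.** It concerns the pooled figure.
- **That country comparison is a failed objective.** Countries appear as a comparison only in the abstract and Discussion, not in section 2.1.

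**What to change.** 1. Replace the sentence in section 2.4 with a statement that the sample size is set by the recruitment window and that achieved precision will be reported for each compared group.
2. Report each specialty, financial-system and economic-class contrast as a percentage-point difference with a 95% confidence interval, judged against a difference of interest fixed before the data are seen. The interval should reflect the weights and, where possible, clustering by distribution network. Chi-square may stay but should not carry the conclusion alone.
3. State that a non-significant result in a small group will not be read as uniform practice.
4. Print the effective number of replies beside every weighted pooled figure.
5. Present country results as descriptive.

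The cost is protocol wording, a few table columns and visibly wide intervals for small groups. No further recruitment is needed.
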